### Intervention

*The Food Friends®* is a research-based preschool program designed to address childhood obesity by establishing healthful eating and physical activity behaviors in preschool-aged children. The program consists of two components: *The Food Friends: Fun With New Foods®* focuses on helping children increasing children’s willingness to try new foods and *The Food Friends: Get Movin’ With Mighty Moves®* aims to enhance preschoolers’ gross motor skill development. The program utilizes constructs of the social cognitive theory, tenets of social marketing, and is embedded within Bronfenbrenner’s social ecological framework [21]. Two study schools will receive the intervention in preschool and elementary school (kindergarten and 1^st^ grade) while the three schools in the control condition will receive standard curriculum.

#### Preschool: The Food Friends ®

*The Food Friends: Fun with New Foods (FWNF)* classroom program is a 12-week intervention developed by Colorado State University [22-26]. The length of the program is critical and was established from literature reviews and our own project evaluation data, confirming that 8–12 experiences are necessary for a child to try and accept a new food [15]. Classroom implementation will include: a 15–20 min nutrition activity 1×/week and opportunities to try new foods 2×/week. Various tactics bring *The Food Friends* to life in a playful and exciting manner. Child-centered activities and supporting materials were developed for 8 food characters and 13 novel foods [22,26]. Eight *Food Friends* characters are central to program themes and materials.

*The Food Friends: Get Movin’ with Mighty Moves (MM)* Classroom Program is 18 weeks in length, and will be conducted 4 days a week for 15–20 min/day, for a total of 72 lessons led by the teacher [27]. Each week will focus on a skill from 1 of the 3 gross motor skill categories: stability (e.g., balance), locomotor (e.g., running and jumping), or ball skills (e.g., throwing and kicking). Early in each week, children will be introduced to a motor skill with movement concepts added as the week progresses. Later in the program, skill patterns, a combination of more than one motor skill, will be incorporated into activities. Creatively, graphics depicting each of *The Food Friends* characters participating in different physical activities are incorporated throughout program materials. They illustrate the different motor skills presented to children as *Mighty Moves*. Both programs will utilize a superhero theme (Super Taster and Mighty Mover) to engage in desired behaviors in a fun and creative manner [27,28].

Teacher training at intervention schools will be conducted for both programs prior to classroom implementation addressing program materials, concepts, and child feeding and activity topics. Feeding topics will include neophobia, eating characteristics of 3- to 5-year olds, role modeling, and how to encourage children to try new foods. Hands-on and participatory activities demonstrate to teachers various ways of teaching motor skills and the *Mighty Moves* activities.

Bilingual home connection materials encourage parents, through a set of Simple Tips, to create an environment that provides children with multiple opportunities to learn about and try new foods at home and to participate with their children in physical activity [24,29]. These tips will be seen repeatedly through child-centered parent materials, including: handouts, placemats, an activity book, trading cards, the *Mighty Moves* musical CD with poster insert.

#### Elementary school: Super Tasters and Mighty Movers

In effort to sustain the preschool behavior changes, the messages from *The Food Friends®* (Super Taster and Mighty Mover) will be extended into early elementary school through a ‘booster’ program. The booster program will consist of a kindergarten and 1^st^ grade curriculum with 5 monthly units. Units will include short reminder activities and lessons that reinforce the program messages learned in the preschool *FWNF* and *MM* programs. Banners and posters will be displayed throughout the school environment, including classrooms, cafeteria, and the gymnasium.

To promote school-based messages in the home environment, five monthly packets of The Super Taster and Mighty Mover Club, will be mailed to 1st grade study participants. Each of the mailings will consist of a child newsletter, a bilingual parent newsletter, and a branded educational enhancer (e.g. jump rope, spatula, etc.).

### Measurements

Assessments for the LEAP study are within and across 3 spheres of the social ecological model (Figure 2). Assessments sent home to parents are available in either English or Spanish.

**Figure 2 F2:**
[figure not shown]
**Conceptual model for the Colorado LEAP study.** This model illustrates a multidimensional approach to addressing healthy growth in young children. The bottom of the figure depicts the intervention’s impact on Eating and Physical activity-related behaviors which then may influence Diet, Physical Activity, and Growth. These behaviors occur in multiple environments (micro-, meso-, & macrosystems; colored boxes) that are influenced by roles and social norms. Individual and environmental characteristics (black font) may interact with behaviors, practices, and/or policies (white font) to influence healthy growth. The items listed in the white font in the Child characteristics and Home environment boxes are the outcome measures used in this study.

### Eating behaviors

#### Taste preference (Willingness to try new foods)

Children’s willingness to try new foods and liking for foods will be assessed via a preference assessment administered to each child [30]. The child will be asked to taste 9 foods in a self-selected order, 5 thought to be familiar foods and 4 thought to be novel foods for most young children. Foods will include jicama, garbanzo beans, grapefruit, Gouda cheese, couscous, spinach, salmon, beets, and pineapple; thus representing sweet and savory foods, fruits, vegetables, protein, foods introduced by *The Food Friends*, known and new foods. Children will rate the food as: “yummy”, “just ok” “yucky” using faces that display these qualities. Food refusals will be recorded, obtaining willingness to try (refusal rate) and a liking rating for each food [30].

#### Food neophobia

The Reaction to Food scale of the Colorado Childhood Temperament Inventory provides caregivers ratings of their child’s neophobia and child temperament related to food and eating [31]. This scale consists of 5 items and assesses children’s food dislikes, including new foods (responses range from 1=“not at all like my child” to 5=“a lot like my child;” range of scores from 5 – 25). The measure is reported to have good internal consistency (α = 0.77), test-retest reliability (r = 0.74) and concurrent validity with other longer measures of child neophobia (r = 0.83 with the Food Neophobia Scale (FNS)) [32]. The FNS (child version) [33], an additional parent assessment of the trait of child neophobia, will be administered to parents. The FNS is a 10 item test that assesses children’s willingness to eat foods (responses range from 1=“Agree Strongly” to 7=“Disagree Strongly” with a range of scores from 10–70). This measure has been validated against behavioral observations of children’s willingness to taste foods (r = 0.38, p ≪ 0.001) and parent predictions of their child’s willingness to try foods (r = 0.34, p ≪ 0.001).

#### Oral sensory characteristics

The Sensory Profile is a 125-item questionnaire which measures sensory processing in 6 different domains, including oral sensory sensitivity [34]. The twelve items that are part of the Oral Sensory Processing scale (e.g. “Avoids tastes or food smells that are typically part of a children’s diet”; internal consistency, α = 0.845) will be utilized for this study. Responses for the Sensory Profile are given on a 5-point Likert scale (Always = 1 to Never = 5) and it has been used and validated with both clinical and non-clinical samples of children [35-37]. Scores for the oral sensory processing scale used in this study can range from 12 to 60 and higher scores relate to typical performance in oral sensory processing and lower scores indicate that there are issues in oral processing.

#### Self concept

The Pictorial Scale of Perceived Competence and Social Acceptance for Young Children (PSPCSA) is a self-report instrument designed to assess perceptions of young children ages four to seven in four domains (i.e., Cognitive Competence, Physical Competence*,* Peer Acceptance, Maternal Acceptance) [38]. The test uses a structured response format that is designed to be sensitive to the developmental capacities of young children, allowing children to identify with test items, and to make meaningful differentiations between possible responses. Each of the four subscales contains six test items for a total test length of 24 items. Oblique factor analyses indicated that intercorrelations among the items for preschool and K-2 children provide evidence of the factorial validity of the instrument. Reliability coefficients fell between .52 and .85. Harter and Pike provided evidence that the PSPCSA showed good convergent, discriminant, and predictive validity in preschool and K-2 children [39].

#### Parent feeding practices and behaviors

Child Feeding Questionnaire v.2 (CFQ) is a self-report measure that assesses child-feeding attitudes and practices and perceptions of the child’s weight. Parent feeding practices are measured using 5 subscales from the original CFQ (Restriction, Pressure to Eat, Monitoring, Concern about Child Weight) and 3 additional scales that have been developed in samples in Colorado (Offering New Foods, Urging New Foods, Concern about Child not Eating Enough). Items are scored on a Likert scale of 1 = Never to 5 = Always. The CFQ has demonstrated good internal consistency, test retest reliability and convergent validity [40].

### Diet

#### Consumption of program target foods

In preschool classrooms, pre-weighed servings (65 ± 2 g) of 2 foods - a program indicator food (jicama) and a novel food (edamame) – will be offered at lunchtime (preschool) or snack time (elementary school) along with other lunch or snack foods. Each child’s target foods will be post-weighed and the amount consumed recorded in g.

#### Food frequency

The Block Kids Food Screener (Ages 2 – 17) will be used to measure parent reports of their child’s food intake. This food screener assesses children’s intake by food group and reports outcomes in number of servings and calories consumed [41,42].

### Healthy growth

#### Anthropometrics

Children’s weight and height will be measured according the method of Harrison and colleagues [43] on a digital scale (Lifesource ProFit UC321; Milpitas, CA) to the nearest 0.05 kg (.1 pounds) and by portable stadiometer to the nearest 0.1 cm (Seca Corp, Hamburg, Germany) by trained research staff. Body Mass Index (BMI) and sex- and age-adjusted BMIz scores will be calculated in the manner documented in the 2000 CDC Growth Charts for the United States [44]. Parental height and weight is collected by self-report, and BMI is calculated.

### Physical activity

#### Physical activity levels and intensity

Pedometers and accelerometers will used to assess physical activity (PA). Two Walk-4-Life pedometer (Model W4L Classic; Plainfield, IL), with safety strap, will be sent home along with a log to record the number of daily steps. Parents will be asked to place the pedometer on the child and themselves when the child/parent gets out of bed and to take it off when the child/parent goes to bed. They will be asked to record the number of total steps taken each day for six days – four weekday and two weekend days. Parents will also be asked to record notes about if the child/parent did not wear the pedometer for a specific time during the day, what types of activities they participated in, etc. A subsample of participants will be asked to wear an Actical accelerometer (Phillips – Respironics, Oregon, USA) to measure time spent in various intensities of PA as well as time spent in activity at school versus home. The accelerometer will be attached on the non-dominant wrist of each student with semi-non-removable band to measure PA. The Actical is a small, lightweight, waterproof, omni-directional accelerometer. It will be placed on the child during the school day. Children will be asked to wear the accelerometer for a 6-day period and to maintain “typical” activity patterns. To encourage compliance in wearing the accelerometers, the children and parents will be given written and verbal instructions.

### Physical activity related behaviors

#### Gross motor skills

The Bruininks-Oseretsky Test (BOT-2) of Motor Proficiency, Second Edition, will be used to assess gross motor development [45]. The BOT-2 is a standardized, norm-referenced measure for children ages 4 through 21 years of age. Reliability and validity of the BOT-2 is reported in the test manual [46]. Four subtests will be performed with children: balance; speed and agility; upper limb coordination (ball skills); and strength. Administration and scoring will be conducted according to the standardized methods described in the manual. Testing time averages between 20–25 min. Raw scores for each sub-test will be calculated and then transformed into standard scores.

#### Parent activity practices and behaviors

This physical activity (PA) survey will be completed by parents. It addresses the parent’s perception of the child’s athletic coordination and enjoyment of PA. The survey also will inquire about parent enjoyment of PA, family support for PA, and importance of the child participating in sports and PA and parent PA, including moderate PA during the previous 7 days, vigorous PA during the previous 7 days, and a self-rating (0 to 10) of parent’s PA level [47]. The survey is a hybrid of the valid and reliable Amherst Health and Activity Study Adult Survey of Child Health Habits used in 5–12 y olds and an adaption of the Amherst Survey used in 3- to 5-y olds [48,49].

### Home and school environments

#### Home food and activity environment

The Home Inventory Describing Eating and Activity (Home IDEA) is a self-report parent survey of the physical home environment. This measure has been modified from an existing measure with established reliability (inter-rater) and validity (criterion and construct) [50-52]. The Home IDEA has been adapted to include a greater variety of foods and drinks, including representation of items for families having low socio-economic resources and living in rural environments. The Home IDEA includes responses for the presence of food and drinks (108 items), PA devices (16 items), and measures the child’s bedroom for the presence of electronic devices (e.g. television; 12 items).

#### Preschool environment

Key preschool staff will complete the Nutrition and Physical Activity Self-Assessment for Child Care (NAP SACC) instrument to identify current center nutrition and physical activity policies and practices. The self-assessment instrument includes 54 items covering nine nutrition and five physical activity areas. Nutrition areas include 37 questions covering such topics as foods offered, menus and variety, feeding practices, education for staff, children and parents; and nutrition policy. Physical activity areas include 17 questions addressing: active play and inactive time; play environment; supporting physical activity; physical activity education for children, parents, and staff; and physical activity policy. The NAP SACC instrument has been used in previous studies measuring nutrition and physical activity policies practices in early childhood settings and has documented evidence of validity and reliability [53-56].

#### School environment

The School Environment and Policy Survey, consists of three modules designed to capture nutrition and physical activity environments, policies and programs offered in the elementary schools. It will be completed by the Principal, Food Service Manager and Physical Education Teacher at each participating school. This instrument covers the following content areas: opportunities for healthy eating in the cafeteria; opportunities for healthy eating outside of the cafeteria; healthy eating policies and practices; increasing physical activity through physical education; increasing physical activity through recess; other opportunities for physical activity; and other school policies and practices [57].

### Demographic information

Parents will also complete an additional questionnaire that supplies demographic information including age, ethnicity, race, education, employment status, and income bracket.

### Data collection

Observational measures of children conducted at the schools and parental responses to the various assessment instruments returned in the parent packet will be aggregated into a single master database using a variety of strategies. While some assessment measures will be collected using traditional paper forms, two other methods have been developed to increase the accuracy while reducing time for data entry into the database.

First, electronic forms designed and implemented in Microsoft Access program running on 8 touch-tablet PCs are used to record child performance or answers during assessments conducted in the school settings. This approach uses a split-database design in which data-entry forms are dispersed as file copies residing on each touch-table PC and all data, organized in several tables, reside in a single back-end Access database file. To upload the data collected on the customized electronic forms, the touch-tablet PCs are networked via Wi-Fi to a notebook computer functioning as an ad hoc router/server where the back-end database file resides. This split-database design eliminates the problem of how to collate the data off each tablet into a unified database.

A second alternative method for electronic data entry was developed for the parent reports when the nature of the responses could be organized to be answered as checked off items. For this approach, we specifically designed the assessments instrument using Microsoft Word software to be electronically scanned using the Remark Office OMR 8 Software (Gravic, Inc., Malvern, PA). Scanned records were then added to the master database.

Finally, to reduce data entry errors all measures recorded on paper forms that have to be manually entered into the database, we designed electronic entry forms in Access to match the appearance of the original paper form. To further ensure the accuracy of entries, measures will be independently entered into a second database file and each measure entered into the master database will be compared to their corresponding second entry. Any discrepancies found will be resolved by referring to the original paper form with the correct values re-entered.

### Data analysis

Data will be analyzed using SPSS 21.0 Windows (IBM SPSS Statistics, Inc., Chicago, IL) program. Descriptive statistics (e.g., percentage, mean, standard error, etc.) will be obtained for demographic, anthropometric, and weight status variables. Additionally, shape-based statistics will be calculated to test assumptions for parametric procedures; data not meeting assumptions will either be transformed or appropriate non-parametric procedures will be utilized. The statistical evaluation associated with the research questions will employ either MANOVA or ANOVA procedures followed by planned comparison t-tests. For example, to answer Question 1 that states *Food Friends®* and *Mighty Moves*™ increase willingness to try new foods and develop motor performance, and that these gains will persist throughout a three year period, a 2x2 MANOVA mixed model design will be used to assess the final outcome measures at the end of the last year. The two factors, are Treatment Intensity (2 levels; experimental and control groups), a between group factor, and Time (2 levels; pre and post treatment), a within group factor. The multiple dependent measures to be explored include the nutrition measures of food preferences, willingness to try, and dietary consumption along with physical activity measures including for example, gross motor skills, pedometer steps and accelerometer outputs. To test the specific hypotheses for Question 1, each dependent variable will be explored using 2x4 ANOVA design (the same factors as above but the within factor, Time, consisting of 4 time periods) followed by orthogonal *a priori* t-tests. Covariates will also be added to the basic ANOVA design to explore effects of age, sex, ethnicity, and location. The significance level will be set at α = 0.05 for all analyses.

To assess whether preference and motor performance directly affect child weight status or serve as mediators to dietary intake and physical activity as they affect child weight (Question 3), three prediction models will be tested beginning with the use of a hierarchical multiple regression analysis. In both prediction models, measures representing concepts of Davison and Birch’s ecological model of child weight status serve as predictors (i.e. independent variables) with measures of child characteristics and child risk factors entered first (step 1), and measures of parenting styles and family characteristics in the next step, (step 2). The prediction models will differ in their inclusion or exclusion in step 1of (a) dietary intake and physical activity measures or (b) taste preference and motor performance or (c) the combination of dietary intake, physical activity measures, taste preference and motor performance. Changes in the beta weights of these variables across the 3 predictor models will be examined to determine the relationships of taste preference to dietary intake and motor performance to physical activity measures.

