**Methods:**

The study is located in 5 rural Colorado preschool centers and elementary schools (2 treatment and 3 control). Treatment sites receive *The Food Friends®* nutrition (12 weeks) and physical activity (18 weeks) interventions during preschool. Observational measures assess 3 layers of the social ecological model including individual, family and organizational inputs. Children’s food preferences, food intake, gross motor skills, physical activity (pedometers/accelerometers), cognitive, physical and social self-competence and height/weight are collected. Parents provide information on feeding and activity practices, child’s diet, oral sensory characteristics, food neophobia, home food and activity environment, height/weight and physical activity (pedometers). School personnel complete a school environment and policy assessment. Measurements are conducted with 3 cohorts at 4 time points – baseline, post-intervention, 1- and 2-year follow-up.

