## Methods/design

### Study design

The Colorado LEAP project is a longitudinal cohort study utilizing a controlled quasi-experimental design in 5 rural Colorado communities. Two communities serve as intervention communities with the other 3 as matched controls. Intervention sites will receive *The Food Friends®* nutrition and physical activity programs in preschool and ‘booster’ programming in kindergarten and 1^st^ grade. Assessments will be administered 4 times - twice in preschool (Fall and Spring) and once in both kindergarten and 1^st^ grade (Spring) (Figure 1). Observational measures of children will be conducted at the school; parent/home measures will be sent home and returned to school via the child; and school personnel will complete school environment and policy assessments. This study was approved by the institutional review boards at Colorado State University and the University of Colorado Denver Anschutz Medical Campus.

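### Five whole communities are allocated (2 vs 3), but the programme-effect tests and the sample size treat children as independent; the 5% error rate and the 90% power hold only if between-community variation is close to nil

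*Protocol article*

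**What the plan says.** The Study design section describes a "longitudinal cohort study utilizing a controlled quasi-experimental design in 5 rural Colorado communities" and continues: "Two communities serve as intervention communities with the other 3 as matched controls". The Intervention section confirms delivery by site: "Two study schools will receive the intervention in preschool and elementary school".

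The Data analysis section sets the method: "The statistical evaluation associated with the research questions will employ either MANOVA or ANOVA procedures followed by planned comparison t-tests". For Question 1 it names a 2x2 MANOVA and then a 2x4 ANOVA for each outcome. The between factor is "Treatment Intensity (2 levels; experimental and control groups), a between group factor" and the within factor is time. The only wording that bears on site is "Covariates will also be added to the basic ANOVA design to explore effects of age, sex, ethnicity, and location". On error control it says "The significance level will be set at α = 0.05 for all analyses".

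The Sample size estimation section uses Cohen's formulas for two groups of children: 90 per group with 90% power for motor skills, 64 per group for BMI, and 100 per group enrolled after 10% attrition. The article nowhere mentions clustering, an ICC, a design effect or a random effect for school or community.

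**The concern.** Treatment varies only between communities. If children in one community tend to change alike, for whatever local reason, the difference between arms carries between-community variance with only two and three independent contributions. A child-level ANOVA or t-test takes its error term from the spread between children, so it omits most of that variance. Standard errors are then too small, and an ordinary difference in change between towns can be declared a programme effect. Research Questions 1 and 2 are both programme-effect claims. The power statement rests on the same assumption of independent children.

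**Working it through.** **Inputs from the document.** 2 intervention and 3 control communities (Study design); 90 analysed children per group, 90% power, 10% attrition, and 64 per group for BMI at an effect size of 0.50 and 80% power (Sample size estimation); α = 0.05 (Data analysis).

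**Assumptions, not in the document.** Two-sided testing; equal site sizes within arm (2 × 45 and 3 × 30); change-score ICC ρ from 0.001 to 0.10; no gain from matching.

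**1. The plan's own figures.** A two-sample t-test at effect size 0.50, 80% power and α = 0.05 needs 63.8, so 64 per group, as printed. 90/(1 − 0.10) = 100 per group, 200 in total, also as printed. The motor-skill effect size is not printed; 90 per group with 90% power implies d of about 0.486. All these figures correspond to independent children, that is, a design effect of 1.

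**2. Variance of the difference in mean change** (total SD = 1).
- Under independence: 2/90 = 0.0222.
- With clustering: V = (1 − ρ)(2/90) + ρ(1/2 + 1/3).
- Example, ρ = 0.05: 0.95 × 0.0222 + 0.05 × 0.8333 = 0.0211 + 0.0417 = 0.0628, which is 2.83 times 0.0222.

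**3. True type I error of the child-level test.** The pooled within-arm variance picks up a little of the between-site variance. Its expectation is w = (1 − ρ) + ρ[(90 − 45) + (90 − 30)]/178. The ratio of true to estimated variance is R = V/(w × 2/90), and the type I error is 2[1 − Φ(1.96/√R)].

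| ICC | V ÷ (2/90) | R | Type I error | Simulated (40,000 runs) |
|---|---|---|---|---|
| 0.001 | 1.04 | 1.04 | 5.4% | – |
| 0.005 | 1.18 | 1.19 | 7.2% | – |
| 0.01 | 1.37 | 1.37 | 9.4% | 9.2% |
| 0.02 | 1.73 | 1.74 | 13.8% | 13.8% |
| 0.05 | 2.83 | 2.88 | 24.8% | 24.4% |
| 0.10 | 4.65 | 4.85 | 37.3% | 37.3% |

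With 100 analysed per group, the error is 9.9% at ICC 0.01 and 39.4% at 0.10.

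**4. Community-level test.** A t-test on the five community means (3 df) had a simulated type I error of 4.4% to 4.9% across ICC 0 to 0.10 with 90 per group. Its power at d = 0.486 comes from the noncentral t with 3 df and noncentrality 0.486/√V:
- ICC 0: 60%
- ICC 0.01: 0.486/√0.0303 = 2.79, power 48%
- ICC 0.05: 0.486/√0.0628 = 1.94, power 28%
- ICC 0.10: 0.486/√0.1033 = 1.51, power 19%

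The plan states 90%. The ICC 0 line shows that part of the loss comes from having only 3 degrees of freedom.

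**Scope of the arithmetic.** It covers a two-group comparison of change, which is the same test as the group-by-time interaction in a 2x2 univariate layout. The multivariate test and the multi-df 2x4 interaction were not computed, but their error terms have the same omission.

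**The case against.** **The ICC is unknown.** This stands. A reader might infer that the false-positive rate simply is 9% to 37%. The document does not support that. The range follows from an assumed ICC of 0.01 to 0.10, and change scores may have a smaller ICC than single measurements. At 0.001 the inflation is negligible. But the document offers no ground for assuming so small a value either.

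**Controls are matched.** Matching may reduce between-community differences. The matching variables are not given, so the gain cannot be sized. The planned analysis does not use the matching, and matching does not make children within a town independent.

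**Location is a covariate.** This does not rescue the plan. If location means community, it is nested in treatment, so a fixed effect for it is aliased with the treatment main effect and gives no between-community error term for change. If it means something else, clustering stays unmodelled.

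**The text mentions a mixed model design and hierarchical regression.** The first is explained on the spot as one between and one within factor. The second is block entry of predictors for Question 3. Neither contains a random site effect.

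**Stronger readings to avoid.** Not every planned analysis is an ANOVA or t-test: Question 3 uses regression, and non-parametric methods are a fallback. As described, these also ignore clustering, but the figures above were not computed for them. The document does not say that children in a community share teachers or meals. The Abstract says "Measurements are conducted with 3 cohorts at 4 time points" without saying how cohorts relate to sites, so no bias in the treatment contrast can be inferred from leaving cohort out.

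**It could be left to an analysis plan.** This does not stand. The article prints the model, its factors, the significance level and the basis for power, and these do not fit the allocation it describes.

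**Conclusion.** The point holds in conditional form. The programme-effect tests and the sample size take the child as the independent unit although five whole communities are allocated. For a change-score ICC of 0.01 to 0.10, with 90 analysed per group and equal sites within arm, the true type I error of the nominal 5% test is about 9% to 37%. It falls to about 7% at 0.005 and near 5% at 0.001. The 90% power holds only for independent children and cannot be delivered by a valid 3-df test at the implied effect size. This should be corrected before analysis, since the p-values for Questions 1 and 2 are reliable only if between-community variation in change is practically nil. A reader might infer that correct standard errors would make a significant result attributable to the programme. They would not: allocation is not random, and confounding by community remains.

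**What to change.** 1. **Primary test.** Replace the child-level test of programme effect by a two-stage analysis: compute each community's mean change for the outcome and time point of interest, then compare the two intervention means with the three control means by a t-test on 3 df, with its confidence interval.
2. **Supporting analysis.** Fit a linear mixed model with treatment, time, treatment by time and cohort as fixed effects, and random effects for child and community (and community by time if all four visits are modelled together). Use Kenward-Roger or Satterthwaite degrees of freedom. With five communities the variance components will be poorly estimated, so this should not be primary.
3. **Location.** Define it. If it means community, do not present it as an adjustment for site in the treatment test.
4. **Reporting.** Give the estimated ICC for each main outcome. Label any child-level p-value as conditional on these five communities.
5. **Power.** State in the Sample size estimation section that 90% power assumes independent children, and give the 3-df figures over a range of ICC.
6. **Interpretation.** State that the correction does not address confounding by community.

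The cost is revised wording and modest analyst time, with no new children or data. The real price is wider intervals and the loss of the 90% power claim.
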